## Abstract

Diabetes generates a great impact on society, as well as a concern for health professionals due to its high and increasing prevalence; there are several studies that demonstrate the effectiveness of vibration platforms and their benefits at a physiological level. The aim of this study will be to analyze the decrease in glycosylated hemoglobin and glycemia levels after the use of whole-body vibration platforms and the possible inclusion of this therapeutic option within the usual treatments. This is a double-blind, randomized controlled trial with parallel group design in a 1:1 ratio. The sample will be composed of people diagnosed with type 2 diabetes mellitus in in the Plasencia area (Cáceres, Extremadura). Participants will be randomly assigned to the intervention or control group using a randomization list and will follow the inclusion criteria: type 2 diabetics between 50 and 60 years of age and not taking diabetes medication. All participants will undergo a determination of glycosylated hemoglobin, blood pressure, lipid profile, weight and height, and different functional tests such as Time Up and Go, 10 Meters Walk Test, and 5 Sit To Stand. The experimental group will perform a whole-body vibration intervention on an oscillating platform for 12 weeks with a weekly frequency of three nonconsecutive days and a duration of 12 min. The exercises will consist of 60 s of work and 60 s with rest. The control group will carry out their normal life insisting on the importance of glycemic controls before and after their daily physical exercise. This study has been registered at clinical.trial.org, ID: NCT 05968222. Whole-body vibration platforms have demonstrated their effectiveness in different pathologies such as stroke, fibromyalgia, sclerosis multiple, or Parkinson’s. For that reason, an improvement in glycemic and lipid values and body composition are expected in people with diabetes after a whole-body vibration intervention for 12 weeks’ duration. In addition, whole-body vibration platforms could be postulated as an alternative to usual treatments.

## 1. Introduction

The human body is subjected to constant vibrations during daily activities that generate a series of negative physiological responses in the organism [1]. The use of vehicles, sports performance, or professional activity with machinery such as hammers can cause injuries. The common characteristics of these vibrations are high intensity, high frequency, and long exposure times. However, the exposure of the human body to low-intensity vibrations and short exposure times has been shown as a training method to be proved to be a tool for improvement of strength and co-ordination [2]. 

In addition, vibration therapy (VT) interventions can be an attractive alternative for people with contraindications to physical activity or manifesting kinesiophobia [3].

There are basically three types of VT: first, the vibration is applied directly to the muscle or the tendon of a muscle by a vibration device or by vibrating cables [4,5] (direct vibration); second, the vibration enters the human body through the hands when gripping a vibrating dumbbell or bar (indirect vibration) (both types of segmental vibration) [5]; and, third, the vibration enters when standing on a vibration platform, so-called whole-body vibration (WBV) [6]

WBV can be applied in treatment using stimuli with specific parameters, such as frequency, amplitude, time, and propagation method [7]. The effects of WVB are based on the fact that vibrations activate muscle spindles, causing their contraction: tonic vibration reflex (TVR) [8]

There are numerous research studies in which WBV has demonstrated efficacy in both healthy populations and in those with health issues. Marín-Cascales et al., 2018 showed that WBV is an effective method in postmenopausal women with osteoporosis (OP), improving bone mineral density (measured in lumbar spine and femoral neck) [9].

It has been proved that vibration therapy applied regularly has a beneficial impact on lowering the level of total cholesterol and LDL cholesterol in people with hypercholesterolemia and in women aged 65 years or more [3].

Therefore, perhaps the use of vibration therapy can be very useful in the pathologies of the elderly, where the passage of time causes functional deterioration of organs, systems and tissues, balance disorders, falls, joint problems, and metabolic disorders (such as diabetes mellitus (DM) and obesity).

DM is one of the most prevalent pathologies. Specifically, worldwide, 536.6 million people suffer from diabetes; in Spain, the incidence of type 2 DM is estimated at one in seven people, which is equivalent to 13.8% of the population (around 5.1 million adults) [10].

DM is characterized by persistently elevated blood glucose levels as a result of impaired insulin secretion, insulin action, or both. According to the American Diabetes Association (ADA) [11], diabetes can be classified into:

Diabetes mellitus type 1 (DM 1): due to autoimmune destruction of β-cells, usually leading to absolute insulin deficiency. Diabetes mellitus type 2 (DM 2): caused by a progressive loss of insulin secretion from β-cells during the course of the disease. Gestational diabetes mellitus (GDM): diabetes diagnosed in the second or third trimester of pregnancy that was not clearly manifest diabetes before gestation. Specific types of diabetes due to other causes, e.g., monogenic diabetes syndromes (such as neonatal diabetes and maturity-onset diabetes of the young), diseases of the exocrine pancreas (such as cystic fibrosis), and drugs or chemicals. Finally, induced diabetes, such as with glucocorticoid use, in the treatment of HIV/AIDS or after organ transplantation.

Diabetes has a great impact on society, and health professionals are concerned about its high and ever-increasing prevalence, not to mention the high cost to the health care system; raising awareness among these people is the key to combating this problem [11].

This fact has led to an increasing number of studies demonstrating vibration platforms’ effectiveness and their benefits at a physiological level, since it has been proven that they improve glycosylated hemoglobin, plasma glycemia, flexibility, contribute to the reduction or elimination of pain, improve blood circulation, increase bone mineral density (BMD), among others [9,12].

Therefore, the following clinical trial is proposed to test the effectiveness of whole-body vibration platforms in type 2 diabetic patients as well as the choice of this physical activity treatment as a possible alternative or complement to the usual treatment.

## 2. Materials and Methods

The hypothesis of this study will be that the use of whole-body vibration has an effect on type 2 diabetes mellitus by decreasing the levels of glycosylated hemoglobin and blood glucose.

The objective of the study will be to analyze the decrease in glycosylated hemoglobin and blood glucose levels after the use of whole-body vibration platforms at baseline and at 12 weeks in people diagnosed with type 2 diabetes mellitus.

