### 2.3. Variables

Anthropometric measurements such as weight, height, and waist–hip ratio will be taken. In addition, functional tests such as Time Up and Go (TUG), 10 Meters Walk Test (10MWT), and 5 Sit To Stand (STS) will be performed. Finally, capillary blood samples will be taken to measure HbA1c and plasma glucose and lipid profile. In addition, blood pressure, weight, and height values will be collectd.

HbA1c is a blood test to determine the average level of glucose or sugar in the blood during the last two or three months [11]. According to the ADA for the diagnosis of diabetes, HbA1c should be at values greater than or equal to 6.5% (≥48 mmol/mol); however, normal HbA1c values should be below 5.7%. The Affinity A1c Analycer^®^ (Debramedix Slne laboratory, Spain)will be used. The HbA1c analysis is a simple test, which consists of obtaining a few drops of capillary blood from a fingertip using a lancet and transferring them to the Affinity A1c Analycer^®^. HbA1c will be taken at baseline and at 12 weeks post procedure to identify variations after VBW.

Regarding capillary glucose, it is a capillary blood glucose measurement using a glucometer (FreeStyle InsuLinx glucometer^®^, Abbott laboratory, Spain) to determine glucose values and facilitate self-monitoring of DM. Obtaining a capillary blood glucose sample is necessary to verify that participants are in optimal conditions to perform the training session (blood glucose levels lower than 90 mg/dl or higher than 250 mg/dl prevent participants from performing the exercises) and also to verify the effect of whole-body vibration (WBV) on the behavior of blood glucose 48 h after the previous session [11].

The LUX^®^ meter (Debramedix Slne laboratory, Spain) will be used for the quantitative measurement of blood parameters such as total cholesterol, HDL cholesterol, and LDL cholesterol (calculated). As with the HbA1c, it is a simple test, which consists of obtaining a few drops of capillary blood from a finger of the hand using an auto-lancet Vitrex Sterilance (Debramedix Slne laboratory, Spain) and pouring them into the LUX^®^ meter. The lipid profile should be below 200 mg/dL for total cholesterol, 40 mg/dL or higher for HDL cholesterol, and less than 100 mg/dL for LDL cholesterol and should be taken at baseline and at 12 weeks after the start of the procedure to identify variations after VBW [13].

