#### 2.5.1. Control Group

Participants in the control group will undergo a determination of glycosylated hemoglobin, blood pressure, lipid profile, weight and height, as well as functional tests such as TUG, 10MWT, and 5STS. Subsequently, they will be encouraged to continue their normal life, insisting on the importance of glycemic controls before and after their daily physical exercise, in addition to continuing with the dietary measures recommended by their specialist. After 12 weeks, glycosylated hemoglobin, blood pressure, lipid profile, weight, height, and the TUG, 10MMT, and 5STS tests will be redetermined.

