#### 2.5.2. Experimental Group

Participants in the intervention group will be subjected to the following tests:-At the beginning of the intervention, a determination of glycosylated hemoglobin, blood pressure, lipid profile, weight, height, and TUG, 10MWT, and 5STS, which will be repeated after 12 weeks of intervention.-Before each training session, participants will undergo a basal blood glucose and blood pressure measurement, which will be repeated after the end of the session.-Each training session on the vibrating platform is composed of 6 exercises, with a duration of 60 s, with 60 s pauses between exercises and a warm-up exercise:

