### 2.6. Study Schedule

During the first week of February, detailed information on the procedure, informed consent, and the schedule of the study interventions will be provided. 

During the second week of February, preintervention measurements of HbA1c, lipid profile, blood pressure, height and weight, and TUG, 10MWT, and 5STS will be carried out so that they can be compared with the postintervention measurements.

During the following 12 weeks, the experimental group will carry out the intervention by means of the exercises in the WBV. These exercises will be performed three days a week, with a rest of at least 24 h between days of intervention.

In the third week of May, after the end of the intervention, the participants will again undergo HbA1c, lipid profile, weight, height, and TUG, 10MWT, and 5STS tests. The control group will also have their blood pressure measured (Figure 2).

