### 2.7. Statistical Analysis

A descriptive analysis will be performed for the experimental and control groups. Similarity between groups will be calculated at baseline and differences between groups at 12 weeks will be examined. The variables HbA1c, lipid profile, weight, height, and blood pressure will be selected in bivariate analyses. Adjustment for confounding factors will be examined by linear regression. Questionnaire scores will be assessed and changes between baseline and 12 weeks between groups will be sought. Statistical analysis will be performed using IBM SPSS statistics version 28.0.

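### Blood glucose is a stated outcome at baseline and 12 weeks, but no visit list schedules it in either group, so as scheduled it has no randomised comparison

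*Protocol article*

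**What the plan says.** Section 2 states the hypothesis that whole-body vibration acts on type 2 diabetes by "decreasing the levels of glycosylated hemoglobin and blood glucose". The objective, in the same section, is to "analyze the decrease in glycosylated hemoglobin and blood glucose levels after the use of whole-body vibration platforms at baseline and at 12 weeks". The aim in the abstract and the conclusions (section 4) again pair glycaemia with HbA1c.

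Section 2.3 says that "capillary blood samples will be taken to measure HbA1c and plasma glucose and lipid profile", without naming a group or a visit. For HbA1c the same section goes on to fix the times: "HbA1c will be taken at baseline and at 12 weeks post procedure". The lipid profile gets a similar sentence; glucose does not. Section 2.5 puts plasma glucose among the determinations that a third researcher makes in the study subjects, again without a visit.

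The lists that tie measurements to a group and a time read differently. For controls: "After 12 weeks, glycosylated hemoglobin, blood pressure, lipid profile, weight, height, and the TUG, 10MMT, and 5STS tests will be redetermined". For the experimental group, the baseline and 12-week list also omits glucose, but a separate item adds: "Before each training session, participants will undergo a basal blood glucose and blood pressure measurement", repeated when the session ends. In the calendar (2.6), at the May visit, "the participants will again undergo HbA1c, lipid profile, weight, height, and TUG, 10MWT, and 5STS tests". In section 2.7: "The variables HbA1c, lipid profile, weight, height, and blood pressure will be selected in bivariate analyses".

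**The concern.** A randomised comparison of glucose needs readings in both groups at a common time. The hypothesis and objective promise a result for glucose, but the operational sections attach it only to training sessions, and the control group has none. A team following the visit lists to the letter would reach May with many glucose values in one group and no planned value in the other.

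One of the two hypothesised outcomes would then have no between-group estimate. What remained would be a before-after trend within the experimental group, which cannot separate the effect of vibration from anything else that changed over the 12 weeks. Section 2.2 describes the study as a pilot meant to supply data for a sample size calculation; it would supply no between-group glucose data for that purpose. A baseline reading that is not taken cannot be recovered later.

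**Working it through.** The document states no figure that could be reproduced here. The check is a cross-reading of every place that lists measurements, followed by a count.

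**1. Where glucose appears**

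| Place in the protocol article | Glucose named? | Group and time given |
|---|---|---|
| Section 2, hypothesis and objective | yes | baseline and 12 weeks; no group |
| Section 4, conclusions | yes (capillary) | no group or visit |
| Abstract, list for all participants | no | – |
| 2.3, general list | yes (plasma) | none |
| 2.3, purpose of the capillary reading | yes | tied to training sessions |
| 2.5, third researcher's duties | yes (plasma) | study subjects; no visit |
| 2.5.1, control, baseline | no | – |
| 2.5.1, control, 12 weeks | no | – |
| 2.5.2, experimental, baseline | no | – |
| 2.5.2, experimental, 12 weeks | no | – |
| 2.5.2, training sessions | yes | experimental only; before and after |
| 2.6, February measurements | no | – |
| 2.6, May measurements | no | – |

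Of the six visit lists in 2.5.1, 2.5.2 and 2.6, 0 name glucose.

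**2. Readings with a stated time**

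Inputs: three sessions a week for 12 weeks (2.6), two readings per session (2.5.2), 20 participants per group (2.2).

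- Experimental: 3 x 12 = 36 sessions; 36 x 2 = 72 readings per participant at most; 72 x 20 = 1,440 for the group at full attendance.
- Control: no explicitly timed reading.

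**3. What a between-group estimate needs**

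The estimate of interest is

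(mean change, experimental) − (mean change, control),

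which uses a baseline and a 12-week mean in each group. For the experimental group, the first and last session readings could stand in, imperfectly, for its two means. For the control group neither mean has a scheduled source. Section 2.5.1 only urges controls to check their glycaemia around daily exercise; nothing says those values are collected or standardised.

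**4. Whether the session readings could serve instead**

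The two purposes that 2.3 gives for the capillary reading are clearance to train and the behaviour of glucose 48 h after the previous session. Both presuppose sessions, so neither has a counterpart in the controls. The series is also restricted: 2.3 bars a session when glucose is below 90 or above 250 mg/dl, so no post-session value follows on those days.

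**The case against.** The strongest reply is that the omission is one of listing, not of intent. Section 2.3 does not limit its plasma glucose statement to one group, and 2.5 assigns plasma glucose to the researcher who measures the study subjects, which naturally covers both groups. The objective itself gives the times. The visit lists are demonstrably incomplete: waist–hip ratio is a stated measurement in 2.3 and appears in none of them, and 2.6 mentions May blood pressure for controls only although 2.5.2 repeats it in the experimental group. Figure 2, the study schedule, is not available and might show glucose.

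Much of this stands. A reader might infer that no control will have a glucose value at all. The document does not establish that; it establishes only that none is scheduled in the text. It is a contradiction between sections, not a demonstrated decision to leave controls unmeasured. It remains a fault, because the sections that staff would follow visit by visit are the ones without glucose, and a figure that listed it would conflict with the text of 2.6.

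The absence from section 2.7 carries little weight by itself. A statistical analysis plan could add glucose, and the same list also leaves out the functional tests. No analysis plan, however, can supply control readings that were not taken.

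It can also be said that HbA1c is the main focus (section 3 says as much) and reflects average glucose over two to three months. That limits the damage to the second glycaemic outcome. It does not remove glucose from the hypothesis and objective.

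**Conclusion.** The point holds as an inconsistency with a real consequence. Blood glucose is promised as an outcome at baseline and 12 weeks and named in general terms as measured, but it is missing from all six visit lists. Its only timed readings are up to 72 per participant in the experimental group, against none explicitly timed in the controls. Carried out as scheduled, the trial has no randomised between-group comparison of glucose. The HbA1c comparison, scheduled in both groups at both times and listed for analysis, is intact.

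This rests on two assumptions: that the visit lists in 2.5.1, 2.5.2 and 2.6 are what staff would follow, and that Figure 2 does not add a glucose reading in both groups.

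One further inference should be avoided. A reader might take the limitations section as a warning that glucose falls from winter to spring, so that an uncontrolled February-to-May trend would be confounded by season on the protocol's own evidence. That section speaks of HbA1c only. The case here needs nothing about season: the lack of a control reading is enough.

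**What to change.** Reconcile the sections in one of two ways.

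- **Keep glucose as an outcome.** Schedule one reading at the February baseline visit and one at the May visit in both groups, under the same conditions (same hour, same fasting state). State whether capillary or plasma glucose is meant, since the document uses both terms. List the reading in 2.5.1, 2.5.2 and 2.6 and, secondarily, in 2.7. Make the between-group comparison at those visits the glucose analysis, and describe the session readings as safety checks and within-group description only.
- **Drop glucose as an outcome.** Remove it from the hypothesis and objective, and bring the abstract and conclusions into line.

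The first option costs two glucometer strips per participant, 2 x 40 = 80 in all, at visits where a finger-prick is already made for HbA1c and lipids, plus a short text edit. This assumes that the glucometer is the intended method; a laboratory plasma sample would cost more. The second option costs only the edit.

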### 2.1. Study Design and Setup

The study is a double-blind, randomized controlled trial with parallel group design in a 1:1 ratio.

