### 2.5. Procedure

Participants with type 2 diabetes will be recruited through talks, on alternate days, at the diabetic association of Plasencia (Cáceres). Those who wish to participate and meet the inclusion criteria will be contacted through a preliminary interview where they will be informed of the methodology, objectives, and process of the study and will be given an informed consent form that must be signed for their inclusion in the study. 

The screening will be performed by two physiotherapists and a research nurse at the University Center of Plasencia. The selected participants will undergo an interview where they will be asked about mobility disability and/or comorbidities incompatible with physical exercise in order to exclude those participants who do not meet the inclusion/exclusion criteria.

The study will be conducted from February 2024 to May 2024 by the aforementioned professionals. Participants will be randomly assigned to the intervention or control group, using a randomization list generated by a computer program. All participants who meet the above criteria will be offered entry into the study and will be given information and the schedule of interventions to participate in the study. Patients will continue with their usual lifestyle. After providing information about the study, they will be randomly included in one of the two groups (intervention or control).

Two of the researchers will be responsible for the correct control of the frequency and amplitude of the vibration platform during the entire intervention and for the correct performance of the exercises proposed for each training session, in addition to the functional tests TUG, 10MWT, and 5STS. A third researcher will be responsible for the determinations and parameters to be measured in the sample subjects (HbA1c and plasma glucose, lipid profile, weight, height, and blood pressure).

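### The trial is labelled double-blind, but participants must know their arm and the researchers who supervise the sessions are also responsible for the functional tests

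*Protocol article*

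**What the plan says.** The Protocol article gives the blinding label twice. The abstract has "This is a double-blind, randomized controlled trial with parallel group design in a 1:1 ratio", and Section 2.1 has "The study is a double-blind, randomized controlled trial with parallel group design in a 1:1 ratio". Neither states who is blinded or how.

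The rest of the article describes these arrangements:

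- **Information given beforehand.** Section 2.5 says of prospective participants that "they will be informed of the methodology, objectives, and process of the study".
- **Control condition.** After baseline measurement, Section 2.5.1 says "they will be encouraged to continue their normal life, insisting on the importance of glycemic controls before and after their daily physical exercise". No sham platform or matched attendance is described.
- **Experimental condition.** Section 2.6 sets 12 weeks of platform exercise: "These exercises will be performed three days a week, with a rest of at least 24 h between days of intervention".
- **Staff who run the sessions.** Section 2.5 makes two researchers responsible for the platform settings throughout the intervention and "for the correct performance of the exercises proposed for each training session, in addition to the functional tests TUG, 10MWT, and 5STS".
- **Other measurements.** Section 2.5 continues: "A third researcher will be responsible for the determinations and parameters to be measured in the sample subjects". It lists HbA1c, glucose, lipids, weight, height and blood pressure.
- **Session-day readings.** Section 2.5.2 adds glucose and blood pressure before and after every session, in the experimental arm only. It does not say who takes them.

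**The concern.** The label describes a property that the described conduct cannot deliver. Readers use such a statement to judge risk of bias, and the Study Limitations section does not correct it: it lists footwear, diet and season, but not blinding.

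The functional tests have most at stake. 10MWT and 5STS are done at the fastest speed the participant can manage, so motivation and encouragement enter the result directly. Under Section 2.5 the responsible staff have trained one of the two arms for 12 weeks. Section 4 (Conclusions) says the study will inform on functional balance and blood pressure, so these measures are meant to be interpreted.

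For HbA1c the route is different. An analyzer gives the reading, but participants who know their arm may change diet or activity, and the limitations section concedes that diet cannot be closely controlled.

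**Working it through.** The article gives no figure for this point, and no alpha, power, effect size or standard deviation (SD). The check is therefore a comparison of sections, taken party by party.

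1. **Participants.** Planned sessions are 12 weeks × 3 per week = 36 in the experimental arm and 0 in the control arm. Participants have been told the methods and aims before randomization, and controls have no sham. All 40 (20 per arm, Section 2.2) must know their group once the intervention starts. **Not blind.**

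2. **Functional-test assessors.** Section 2.5 gives the same two people the sessions and TUG, 10MWT and 5STS. Having supervised the experimental arm, they know at 12 weeks who was trained. This covers 3 of 3 functional tests. **Not blind.** At baseline the article does not say whether they know the allocation, and sessions have not yet begun.

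3. **Third researcher.** Section 2.5 gives this person glucose and blood pressure in general. Section 2.5.2 has both taken around every experimental session, without naming anyone. If the third researcher takes them, the allocation is exposed. If someone else does, it need not be. **Not established either way**, and no masking is stated.

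4. **How far each outcome is exposed.**
   - 10MWT and 5STS (Section 2.3): maximal-speed tests with no timing device named. Most exposed.
   - TUG (Section 2.3): run by a phone application with an acoustic start, so tester timing matters less. Effort and encouragement still act.
   - Blood pressure (Section 2.3): aneroid device, reader-dependent. Exposed only if the reader knows the arm.
   - HbA1c and lipids (Section 2.3): meter or analyzer readings. Little room for assessor bias; participant behaviour remains a route.

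5. **Illustration of scale, on assumed shifts.** Suppose there is no true effect, but unblinded effort or assessment moves the group difference by *b* SD. With 20 per arm, SE = √(2/20) = 0.316 SD. A two-sided 0.05 z-test then rejects with probability Φ(*b*/0.316 − 1.96) + Φ(−*b*/0.316 − 1.96):

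| Assumed *b* (SD) | Rejection rate with no true effect |
|---|---|
| 0 | 5.0% |
| 0.1 | 6.2% |
| 0.2 | 9.7% |
| 0.3 | 15.8% |
| 0.5 | 35.3% |

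The values of *b*, the 0.05 level and the z-test are assumptions. The table shows what a shift of a given size would do. It is not evidence that a shift of that size will occur.

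**The case against.** The strongest reply is that the outcomes most exposed are not the trial's target. The hypothesis and objective in Section 2 concern HbA1c and blood glucose, which are read by an analyzer and a glucometer. Section 2.7 does not list TUG, 10MWT or 5STS among the variables for bivariate analysis, and Section 2.2 calls the study a pilot. This stands as a limit on the consequence: the case for assessor bias in HbA1c is weak. It does not rescue the label, which is wrong as written whichever outcome is considered.

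A reader might also infer stronger things that the article does not support:

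- **That nobody in the trial is blind, and that blood pressure in all 40 participants is read by someone who knows the arm.** Section 2.5.2 does not name who takes the session-day readings. A masked third researcher is not ruled out, only not stated.
- **That the supervising researchers time all the functional tests by hand.** Section 2.5 makes them responsible for the tests, and an application runs TUG.
- **That every bias favours the intervention.** This is a reasonable expectation for the functional tests, but it is not shown. For HbA1c, controls know their arm and are reminded of glycemic checks and dietary measures (Section 2.5.1), so their behaviour could move the contrast the other way.

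Nor is this a detail that a journal article leaves to a fuller protocol. The article itself states the label, the control condition and the staff duties, and these conflict.

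**Conclusion.** The point holds for participants and for the functional-test assessors, and those two are enough to make the double-blind label incorrect in the abstract and in Section 2.1. The status of the third researcher is open.

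All 40 participants and the assessors of all three functional tests are affected. The bias in any result cannot be sized from the article. For the functional tests its likely direction favours the intervention, and a larger sample would not remove it. For blood pressure, bias is possible and depends on who takes the session-day readings. For HbA1c and lipids, assessor bias is small, but behaviour change in participants who know their arm cannot be excluded.

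The conclusion assumes only that staff duties are carried out as Section 2.5 describes them and that controls receive no undescribed sham.

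**What to change.** 1. Delete the double-blind label in the abstract and Section 2.1 and call the trial open-label.
2. Reassign the three existing researchers in Section 2.5. The two trainers take the session-day glucose and blood pressure. The third researcher is kept away from sessions, is not told the allocation, and does all baseline and 12-week measurements, including TUG, 10MWT and 5STS. Participants are asked not to reveal their group.
3. Use assessor-blinded only for outcomes actually measured this way. If the duties are not swapped, report those outcomes as unblinded.
4. Reconcile the timing of the functional tests. The end of Section 2.3 ties them to the beginning and end of each session, whereas Sections 2.5.2 and 2.6 place them at baseline and 12 weeks. The revised text must make clear which tests are the outcome tests, so that the masked researcher performs those.

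The cost is new wording and a swap of duties, with no extra staff. The third researcher has a longer test week. Session-day glucose, which Section 2.3 also uses to examine the effect of vibration, would then be recorded by unblinded staff and should be reported as such.

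The swap protects the assessment only. Participants will still know their arm, so effort on the functional tests and behaviour affecting HbA1c remain limitations to state.
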